Hypothesis 2. Including a pedometer as a self-monitoring tool as part of adapted physical activity guidelines will result in a higher likelihood of achieving DG physical activity recommendations (as measured by accelerometer) than an education program alone.

Non-Hypothesis 3. Determine the number of steps (as measured by pedometer) associated with reaching the DG physical activity (as measured by accelerometer) recommendations.

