**Waist Circumference**

**Procedure**

Instruct the participant to gather his or her shirt above the waist, cross the arms, and place the hands on opposite shoulders. Demonstrate the desired position of the arms. It may help to tell participants to think of giving themselves a hug. If necessary, lower the pants and underclothing to slightly below the waist. Again, always tell the participant what you are going to do before you do it.

Stand on the participant’s right side. Palpate the hip area to locate the right ilium of the pelvis. With the cosmetic pencil draw a horizontal line just above the uppermost lateral border of the right ilium. Cross this mark at the midaxillary line, which extends from the armpit down the side of the torso. Exhibit 3-9 shows the measurement site correctly marked for the waist circumference.

Extend the measuring tape around the waist. Position the tape in a horizontal plane at the level of the measurement mark, and ensure the horizontal alignment of the tape. Check that the tape sits parallel to the floor and lies snug but does not compress the skin. Always position the zero end of the tape below the section containing the measurement value. Take the measurement to the nearest 0.1 cm at the end of the participants.

4. Physical Activity Assessment. Study participants will be asked to respond to a physical activity readiness questionnaire (PAR-Q) [Appendix E) for safety reasons before beginning any physical activity regime. Accelerometers and Pedometers will be provided and used to measure physical activity and to increase steps.

Acceleromter Procedure

The ActiGraph accelerometer will be used to determine physical activity at baseline and at follow-up as follows:

The measurement of physical activity pattern and volume, specifically minute-by-minute participation in different intensities of physical activity. The equipment used is the ActiGraph GT3X manufactured by ActiGraph, of Ft. Walton Beach, FL ([www.theactigraph.com](http://www.theactigraph.com/)), and previously distributed as the GT1M, the 7164, the MTI, and the CSA. An ActiGraph User Manual is also available for download from this website.

Process Overview

1. Charging accelerometer
2. Initializing accelerometer (preparing the device to collect data)
3. Instructing the participant on self-monitoring procedures
4. Downloading data
5. Preparing electronic files for archiving

Procedure

1. Charging accelerometer

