**Statistical Analysis**

Analyses will be performed using SAS software. In the case of missing data, several approaches will be used, including an analysis restricted to participants with complete data; a last observation carried forward analysis, and a mixed model analysis. Sensitivity of analytical results to these alternative approaches will be assessed. Statistical tests that result in p-values ≤0.05 will be considered indicative of statistical significance.

The focus of the statistical analysis for **Hypothesis1** will be on comparing intervention and control groups with respect to changes in accelerometer-measured physical activity from the 7-day baseline (pre-intervention) assessment to the 7-day follow-up (post-intervention) assessment. Physical activity (minutes of moderate-to-vigorous physical activity) will be summarized as group means and 95% confidence intervals, separately for baseline and follow-up assessments. Student’s t-test will be used to assess statistical significance of differences in group means for individual physical activity change scores = post-score ─ pre-score. Although this is a feasibility study, we feel that a clinically significant increase in number of daily minutes of moderate-to-vigorous physical activity in this sedentary population would be a 100% increase.

The focus of the statistical analysis for **Hypothesis 2** will be on comparing intervention and control groups with respect to possible increase in percentage of participants achieving DG physical activity recommendations. The (nonparametric) permutation test will be used to assess differences in change in percent achievers in intervention vs. control groups (the sample sizes in this feasibility study are not sufficient to justify employing chi-square tests). Although this is a feasibility study, we feel that a clinically significant increase in the proportion of participants achieving the DG physical activity recommendations will be a doubling of the baseline proportion.

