The focus of the statistical analysis for **Non-Hypothesis 3** will be on determining the number of steps associated with reaching the DG physical activity recommendations of 60 minutes a day of moderate-to-vigorous physical activity. General linear mixed models will be used to assess the cross-sectional relationship between daily number of steps (from pedometer) and minutes of moderate-to-vigorous physical activity (from accelerometer) using data collected post-intervention on all subjects in the intervention group. A mixed model approach is required to incorporate all seven days worth of data collected on each participant. The number of steps corresponding to 60 minutes of moderate-to-vigorous physical activity will be determined, and potential gender differences in the target number of steps will be examined. If significant gender differences exist, gender-specific step targets will be calculated and used in the future effectiveness study.

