# Steps to Increase Physical Activity

# Study Specific Questions

## Adults (Males & Females) BMI **25 – < 35**

**Age 35-64 years**

### Design: 60 Volunteers (30 control group; 30 intervention group) for 3 weeks, 7 days each week.

#### YES NO

1. Do you have heart disease? ____ ____

2. Do you have diabetes? ____ ____

3. Do you have high blood pressure? ____ ____

If so, what medication are you on? **(Hytrin excludes) ____________________________**

4. Are you on cholesterol medication? ____ ____

5. Are you on a medically supervised diet? ____ ____

6. Have you ever been diagnosed with an eating disorder? ____ ____

7. Have you ever had a stroke? ____ ____

1. Have you ever been diagnosed with cancer? ______ ______

9. Have you ever had Hepatitis B, C, or HIV? ____ ____

10. Do you have or ever had tuberculosis? ____ ____

11. Are you currently enrolled in any other study? ____ ____

12. Are you planning to move from area in next 30 days? ____ ____

13. Has your doctor told you to limit physical activity? ____ ____

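### The Hypothesis 2 permutation test on change in achiever status is valid but conservative and inefficient; adjusting follow-up status for the baseline activity minutes already collected gives more power at no data cost

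*Protocol*

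**What the plan says.** Hypothesis 2 in the Introduction is that adding a pedometer "will result in a higher likelihood of achieving DG physical activity recommendations (as measured by accelerometer) than an education program alone". The Statistical Analysis section turns this into a comparison of arms on "possible increase in percentage of participants achieving DG physical activity recommendations" and fixes the test: "The (nonparametric) permutation test will be used to assess differences in change in percent achievers in intervention vs. control groups". It rejects chi-square tests because the samples are small. The effect regarded as clinically significant "will be a doubling of the baseline proportion". The decision rule covers all tests: "Statistical tests that result in p-values ≤0.05 will be considered indicative of statistical significance".

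The accelerometer procedure states: "The ActiGraph accelerometer will be used to determine physical activity at baseline and at follow-up". The Intervention Phase section has both arms wear the device for seven days at each time. Baseline minutes of moderate-to-vigorous physical activity (MVPA) therefore exist for both arms, but the Hypothesis 2 analysis does not use them as a covariate. Appendix C gives the size: "60 Volunteers (30 control group; 30 intervention group) for 3 weeks, 7 days each week". The plan for the step-count question refers to "DG physical activity recommendations of 60 minutes a day of moderate-to-vigorous physical activity". The protocol gives no baseline achiever rate, no pre/post correlation and no power figure.

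**The concern.** In a randomised trial, whether pedometer users are more likely to achieve the recommendation can be answered from follow-up status, with baseline used to remove between-person variation. The stated test subtracts baseline status instead, and this has two costs.

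- **Discreteness.** A score with three possible values, mostly zero, gives heavily tied permutation distributions. The attainable p-values are coarse, and the test rejects well below 5% under the null.
- **Unused information.** Cutting minutes at a threshold weakens the link between baseline and follow-up, and subtraction gives baseline status a fixed coefficient of 1 whatever its predictive value. How far a person was from the threshold at baseline is not used.

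Hypothesis 2 is one of only two between-arm tests, and its result is meant to inform a later effectiveness trial. An avoidable false negative could mislead that design.

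**Working it through.** **Inputs.** From the protocol: 30 per arm (Appendix C); threshold 0.05, target effect a doubling of the baseline rate p0, and the stated test (Statistical Analysis). Assumed, because not given: two-sided testing, p0 of 2% to 40%, correlation rho of 0.3 to 0.9 between baseline and follow-up MVPA on a latent normal scale, no dropout and, unless stated, a control arm that stays at p0. There is no planned power figure to reproduce.

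**Variance.** Let phi be the correlation between baseline and follow-up status, with equal rates p.
- Change in status: 2p(1-p)(1-phi)
- Follow-up status alone: p(1-p)
- Follow-up status adjusted for baseline status: p(1-p)(1-phi²)

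The ratio of change to adjusted is 2(1-phi)/(1-phi²) = 2/(1+phi). From bivariate normal probabilities, rho 0.5 in minutes becomes phi of about 0.20 at p = 5% and 0.32 at p = 30%, so the ratio is 2/1.20 = 1.67 to 2/1.32 = 1.52. Over rho 0.3 to 0.7, phi runs from 0.10 to 0.48 and the ratio from 1.8 to 1.35. Change is noisier than follow-up status alone when 2(1-phi) > 1, that is, when phi < 0.5; this corresponds to latent rho below about 0.7.

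**Power simulation.** Bivariate normal MVPA was cut at the achiever threshold, with 30 per arm, 999 permutations and up to 2,000 trials per scenario. The adjusted test uses residuals from a pooled linear regression of follow-up status on baseline MVPA. The size-equalised column breaks ties at random, so that both tests have their full 5% level. Power in %, stated test vs adjusted test; gaps in points, taken before rounding:

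| p0 to 2·p0 | rho | as planned | gap | size-equalised | gap |
|---|---|---|---|---|---|
| 2 to 4 | 0.6 | 0.2 vs 6.4 | 6.2 | 5.5 vs 7.4 | 1.9 |
| 3 to 6 | 0.6 | 1.2 vs 7.6 | 6.4 | 7.1 vs 7.8 | 0.7 |
| 5 to 10 | 0.5 | – | about 6 | 9.7 vs 10.7 | 1.0 |
| 10 to 20 | 0.5 | 8.8 vs 20.8 | 12.0 | 15.0 vs 20.8 | 5.7 |
| 10 to 20 | 0.8 | 9.3 vs 22.3 | 13.0 | 18.4 vs 22.3 | 3.9 |
| 20 to 40 | 0.3 | 21.0 vs 40.3 | 19.4 | 27.1 vs 40.3 | 13.2 |
| 20 to 40 | 0.5 | 22.9 vs 43.3 | 20.4 | 31.4 vs 43.3 | 11.8 |
| 20 to 40 | 0.7 | 28.1 vs 50.6 | 22.4 | 36.7 vs 50.6 | 13.8 |
| 30 to 60 | 0.3 | 40.0 vs 67.8 | 27.8 | 48.4 vs 67.8 | 19.5 |
| 30 to 60 | 0.5 | 47.0 vs 70.9 | 23.9 | 54.6 vs 70.9 | 16.3 |
| 30 to 60 | 0.8 | 61.7 vs 85.4 | 23.7 | 70.8 vs 85.4 | 14.6 |
| 40 to 80 | 0.3 | 63.0 vs 91.6 | 28.6 | not run | – |

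The Monte Carlo standard error of one power figure is about 1 point: √(0.433 × 0.567 / 2000) = 0.011. Repeat runs differ by that order.

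**Share due to discreteness.** At 20% to 40%, rho 0.5: (20.4 - 11.8)/20.4 = 42%. At 10% to 20%, rho 0.5: (12.0 - 5.7)/12.0 = 53%. At 5% to 10%: (6 - 1)/6 = 83%.

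**Null.** Stated vs adjusted rejection: 1.5% vs 5.1% (10% in both arms, rho 0.5), 2.5% vs 4.8% (20%, rho 0.5) and 2.4% vs 4.8% (30%, rho 0.7). The gain is not bought with an inflated error rate.

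**Control arm also improves (rho 0.6 in these three).** Baseline 10%, control 15%, intervention 30%: 18.1 vs 32.8, gap 14.7. Baseline 20%, 25% vs 40%: 16.0 vs 27.4, gap 11.4. Baseline 30%, 40% vs 60%: 23.5 vs 41.1, gap 17.6. For a small effect (baseline 10%, 15% vs 20%) the test powers are 4.7 vs 8.5, gap about 4. Across repeat runs of such cases the range is about 4 to 19.

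**Change score vs ignoring baseline.** At 20% to 40%, change vs follow-up status alone is 21.3 vs 30.4 at rho 0.3, 28.4 vs 28.3 at 0.7 and 41.3 vs 29.7 at 0.9.

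**The case against.** The best defence is that nothing here is wrong. The planned test controls its error rate, tests what the protocol says it will test, and matches a benchmark expressed relative to baseline. The study is a feasibility study with no power target to miss. The participants are called sedentary and the threshold is 60 minutes a day, so the achiever rate may be low, and there both tests are nearly powerless: at 5% to 10% the size-equalised powers are 9.7% and 10.7%. Both arms receive education, so the control rate may rise, which shrinks the gap. The model also favours adjustment, because it assumes complete baseline data and one clean cut. Appendix F states the recommendation in terms of most days of the week, and a day-count rule was not simulated.

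Much of this stands and limits the size of the point. It does not remove it: the protocol commits to a formal test at 0.05, the adjusted test had more power in every non-null scenario run, and the data are already collected.

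A reader might infer three stronger things that the documents do not support:
- That the test is invalid or biased. It is conservative.
- That the whole gap is information lost by subtracting a noisy baseline. A large share is discreteness.
- That subtracting baseline status is always worse than ignoring it. This holds only below a latent correlation of about 0.7, and the protocol gives no correlation.

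**Conclusion.** The point holds as one of efficiency, and the change is worth making. For a doubling from 2%–40% with an unchanged control arm, the baseline-adjusted permutation test gains about 6 to 29 points; it gains about 4 to 19 in the cases run where controls also improve. With size equalised, the gain for a doubling is about 1 point at 5% to 10%, 4 to 7 at 10% to 20%, 11 to 14 at 20% to 40% and 15 to 20 at 30% to 60%. At baseline rates of 5% or less the benefit is almost entirely relief from discreteness.

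All of this rests on assumed achiever rates, an assumed correlation, the latent normal model and complete data.

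Nor should the change be read as rescuing power. For a doubling, adjusted power was about 40% to 61% from a 20% baseline rate over rho 0.3 to 0.9, 54% to 80% from 25%, and 69% to 91% from 30%. It stays low unless the baseline rate is about 25% to 30% or more.

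**What to change.** Replace the Hypothesis 2 test sentence in the Statistical Analysis section so that it specifies the following:

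1. Regress follow-up achiever status (0/1) on baseline MVPA minutes with arms pooled. Use ranks or log(minutes + 1), because minutes can be zero.
2. Take the residuals and permute arm labels, using the between-arm difference in mean residual as the test statistic.
3. Report the baseline-adjusted difference in follow-up percent achievers with its 95% CI.
4. Keep change in percent achievers by arm as a descriptive summary.

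The cost is one amended sentence and a few lines of SAS. No participants, visits or measurements are added. Participants without a valid baseline week need the missing-data handling already planned, as they would for the change score.

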## **EXPECTED RESULTS**

- Increased knowledge,
- Positive behavior change, and
- Improved health effects in the short and long term.

The new knowledge obtained from this research will inform research, public policy and public health efforts to prevent obesity and its related disorders in the LMD. The results of this project will produce innovative models for understanding the influences on behaviors impacting energy imbalance and procedures for promoting changes in these variables. This information will allow national, regional, state, and local policy makers to better prioritize the use of resources to address the obesity epidemic in the LMD. Viewed from a wider perspective, the results from the studies in this population will inform other researchers in areas of the United States working with rural populations who also present with high levels of poverty and issues regarding food access and availability and problems achieving recommended physical activity recommendations.

# HUMAN SUBJECTS

The inclusion and exclusion criteria for the feasibility study are designed to maximize the number of participants who are eligible to participate, while maintaining the safety of the participants and the ability of the feasibility study to inform the development of the effectiveness trial in Phase II of the research project.

# Inclusion Criteria

Male or female living in Pointe Coupee Parish and:

- age 35 -64 years
- body mass index (BMI) 25 to < 35 kg/m2
- physically capable of undertaking physical activity
- have the capability and willingness to give written informed consent,
- understand exclusion criteria, and
- accept the randomized group assignment

**Exclusion Criteria**

The Study Physician, [name], and Principal Investigator may exclude individuals from the study for any or no reason.

A past history and/or physical examination or laboratory findings of a medical condition including (but not limited to):

- - Cardiovascular, respiratory, gastrointestinal, neuromuscular, neurological, or psychiatric conditions.
  - Musculoskeletal problems interfering with exercise.
  - Immunodeficiency diseases or a positive HIV test.
  - Malignancies in the past 5 years, with the exception of skin cancer therapeutically controlled.
  - Any other medical condition or disease that is life-threatening or that can interfere with or be aggravated by exercise

**Recruitment and consent procedures.** The Institutional Review Board and the Data Safety Monitoring Board will approve all procedures and study protocol at the Pennington Biomedical Research Center. Upon enrollment, each participant will be asked to sign an approved written informed consent form which details the purpose of the study, requirements for participation, and the potential benefits and risks. It will also indicate that participation is voluntary and may be terminated at any time.

**Sources of research material.** The procedures for obtaining research materials will include interviews, and questionnaires. Trained and qualified staff will perform these tasks. Data will be confidentially collected directly from study participants, to be used specifically for research purposes. All information and response to intervention will be documented in each participant’s permanent record with a unique identification number. No identifying information will be released from the study site. All information will be treated as confidential.

**Gender and minorities.** The study population will consist of adults (male and female) of all races, age 40-64 years. Children and adolescents will not be included in this study because the intervention strategy and materials are not

appropriate for this age group.

**Privacy.**  Privacy in the context of this study includes confidentiality of data and personal information. During interviews and measurements, the study staff will ensure full privacy of participants and will ensure that the data are stored in a secured area.

**Right-to-know.** All information obtained from each participant will be available to that participant.

**DOPRU 30-day Feasibility Phase I**

**TIMELINE***

| **Date** | **Activity** |
| --- | --- |
| January 4, 2010 | Meet with community/Recruitment begins |
| January 7, 2010 | Preliminaries/Training of staff, etc. |
| January 14, 2010 | Screening/enrollment first 7 days |
| January 21, 2010 | Feasibility study begins |
|  |  |

## ***Subject to change**

###### Appendix A

Study Flyer

**The Pennington Biomedical Research Center**

**Wants YOU!**

**The Pennington Center is planning to conduct a study**

**in**

**Pointe Coupee Parish**

**to determine ways in which**

**physical activity can be introduced to the**

**Lower Mississippi Delta community.**

**Participants must be between**

**the ages of 35 - 64,**

**a little overweight, and capable of**

**engaging in physical activity.**

**Other exclusions apply and**

###### Appendix B

Initial Screening Form

| Steps to Increase Physical Activity  INITIAL SCREENING |  |
| --- | --- |

Study Name: Steps To Increase Physical Activity Study Number:

Last Name: | | | | | | | | | | | | | | | | | | | |

First Name: | | | | | | | | | | | | | | | | | Middle Initial | |

______________________________________________________________________________________

Mailing Address: | | | | | | | | | | | | | | | | | | | | | | | | |

Apartment: | | | | | Zip Code: | | | | | |

City: | | | | | | | | | | | | | | | | | | | | State: | | |

______________________________________________________________________________________

Home Telephone Number: | | | | - | | | | - | | | | |

Work Telephone Number: | | | | - | | | | - | | | | | Extension: | | | | |

Calling Notes: ______________________________________________________________________________________

Email Address: | | | | | | | | | | | | | | | | | | | | | | | | | |

______________________________________________________________________________________

Date of Birth: | | |  **/** | | | **/** | | | | | Age: | | |

MM DD YYYY

Are you a twin? Yes No Gender: Male Female

______________________________________________________________________________________

Are you of Hispanic origin such as Mexican-American, Puerto Rican, or Cuban? Yes No

What do you consider your race to be? White Black Asian

American Indian, Aleutian, Alaska native, or Eskimo

Pacific Islander Don’t Know

Other _____________________________________

Are you a U.S. Citizen? Yes No If no, Visa? __________________ No Answer

What is your Marital Status? Never Married Married Widowed Separated Divorced No Answer

Do you have high blood pressure? Yes No Family history of high blood pressure? Yes No

Do you have diabetes? Yes No Family history of diabetes? Yes No

Have you ever been diagnosed with breast or colon cancer? Yes No Family history of cancer? Yes No

Height: | | ft. | | | in Weight: | | | | lbs BMI: | | |

Has anyone in your family had a heart attack before the age of 50? Yes No

What is your cigarette smoking history? Never Formerly Current

How often do you drink wine, beer, or liquor? Never Daily Once a Week Less than 2 per month

____________________________________________________________________________________________________________

Are you taking any medications (including hormones or contraceptives? Yes No

If yes, what medications are you taking? _________________________

# FEMALES ONLY

Can you still have children? Yes No

If no, why not? Complete Hysterectomy Partial Hysterectomy

Postmenopausal Tubal Ligation

Other; cause ___________________________________

How did you learn of the study? Flyer Radio TV Newspaper Screening Event / Presentation Word of Mouth

Mailout / Brochure Billboard Email / Website Other: _________________________________

Telephone Screening Status: Eligible ( I) Rejected ; Reason for Reject: Heart Disease Diabetes

High Blood Pressure Cholesterol Medications

Diet Eating Disorder

Stroke Cancer

Medical History Other Study

Moving Limited Physical Activity

Recent Pregnancy Other __________________

Interviewer Initials: _________ Interview Date: _______________________

